### Data management {19}

Trial-related data will be recorded timely using the Electronic Data Capture (EDC) system by research staff only and password-protected access after necessary EDC training. A data manager will supervise routine accuracy checks and address any issues with investigators. Once the data are declared clean, the chief investigator must complete the signature panel associated with each subject and lock the data at the end of the trial. Hard-copy documents outside the EDC system will be stored securely, and electronic files will have password protection. All documents will be saved for at least 5 years post-publication, with original data available upon request to the chief investigator (CI).

### Confidentiality {27}

Personal information will remain confidential. Prior to consent, the name and contact details of the potential participant are shared with the research team and recorded separately. Each participant will be allocated a unique trial ID, and all data will be stored according to this trial ID.

### Plans for collection, laboratory evaluation, and storage of biological specimens for genetic or molecular analysis in this trial/future use {33}

Peripheral blood and specimens of the resected tumor and precancerous tissue will be freshly stored in liquid nitrogen for genetic analysis to screen potentially sensitive populations to neoadjuvant therapy.

## Statistical methods

### Statistical methods for primary and secondary outcomes {20a}

Primary efficacy will be assessed in all randomized patients using the intention-to-treat (ITT) principal. And the safety analysis will include all participants who received at least one post-randomization measure. Kaplan-Meier method is used to determine RFS and OS. Hazard ratios (HRs) with 95% confidence intervals (CIs) are estimated using Cox proportional risk models. Continuous variables are analyzed using either unpaired Student’s *t*-test or the Mann-Whitney *U* test, while categorical data are assessed using the chi-square test or Fisher’s exact test, as appropriate. Data analysis will be performed using SPSS version 26.0 and *P* values < 0.05 are considered statistically significant. The flow of participants screened by the trial and trial results will be reported according to Consolidated Standards of Reporting Trials (CONSORT).

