### Objectives {7}

The study aims to (1) directly compare the efficacy of neoadjuvant therapy followed by surgery and surgery alone on HCC recurrence risk and survival in patients with single huge HCC; (2) explore the safety of neoadjuvant therapy regimen of TACE, camrelizumab, and apatinib; and (3) offer evidence and guidance for neoadjuvant therapy strategy in HCC patients with a high risk of recurrence.

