### Outcomes {12}

The primary endpoint is the 1-year RFS rate, defined as the time period from randomization to the first documented HCC recurrence or death from any cause. The key secondary endpoints include pathological remission degree and OS which was defined as the time period from randomization to death from any cause. Pathological complete remission (pCR) is defined as existent ≤ 1% active tumor cells, while major pathological remission (mPR) is defined as ≤10% active tumor cells. Safety outcomes encompass adverse events (AEs), defined as the occurrence of ≥ 3 grade hematological or non-hematological toxicities (including but not limited to liver dysfunction, hematological abnormalities, hypertension, diarrhea, proteinuria, hand-foot syndrome, etc.). The severity of adverse events will be graded according to the Common Terminology Criteria for Adverse Events (CTCAE v5.0).

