### Sample size {14}

The sample size was performed using the software PASS (version 2015). The calculation is based on the primary endpoint which is RFS in the present study. Previous research data showed that the 1-year RFS rate was 40% for patients with a single huge HCC after surgery [9]. Our prior study showed that the 1-year event-free survival (EFS) rate was 65% for patients with unresectable HCC after receiving a similar treatment regime [22]. Therefore, we hypothesize that neoadjuvant therapy could increase the 1-year RFS rate to 70% for patients with a single huge HCC. Using an alpha of 0.025 at one-sided, a power of 80%, a total of 60 participants needed to be enrolled with 30 in each arm when considering an attrition rate of 10% and an anticipated recruitment period of 1.5 years.

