## Data collection and management

### Plans for assessment and collection of outcomes {18a}

All investigators and coordinators will receive specialized training for data collection. Baseline assessments will be conducted before randomization. Any AE during neoadjuvant therapy will be assessed and managed by investigators and recorded timely. Tumor response after neoadjuvant therapy will be performed via enhanced CT using the response evaluation criteria in solid tumors, version 1.1 (RECIST 1.1), and the modified response evaluation criteria in solid tumors (mRECIST) in 2 weeks after neoadjuvant therapy. Perioperative data, including intraoperative information and postoperative complications which will be graded by Clavein-Dindo criteria, will be recorded before discharge.

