### Methods in analysis to handle protocol non-adherence and any statistical methods to handle missing data {20c}

As we target the treatment regimen estimate, we will include all participants in the primary analysis including those who do not adhere to the protocol. A supplementary analysis will be performed using a per-protocol principal to estimate the treatment effect for those who switch to another arm after randomization. Participants who have missing data points will be included in the analysis under a Missing at Random assumption implicit when using the longitudinal model.

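### The safety set is not tied to receiving trial treatment, so never-treated patients may enter the regimen's denominator and treated patients may drop out of it

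*Protocol article*

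**What the plan says.** The second objective (Objectives {7}) is to "explore the safety of neoadjuvant therapy regimen of TACE, camrelizumab, and apatinib". The outcomes section ({12}) sets the target: "Safety outcomes encompass adverse events (AEs), defined as the occurrence of ≥ 3 grade hematological or non-hematological toxicities".

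The statistical methods section ({20a}) gives efficacy and safety separate sets. For efficacy: "Primary efficacy will be assessed in all randomized patients using the intention-to-treat (ITT) principal". For safety: "the safety analysis will include all participants who received at least one post-randomization measure". It does not say whether safety data are grouped by assigned arm or by treatment received, and no other section makes a dose or a procedure the condition for entering the safety set.

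The section on non-adherence and missing data ({20c}) keeps non-adherent participants in the primary analysis. It adds a per-protocol analysis "to estimate the treatment effect for those who switch to another arm after randomization". Departures from assignment are therefore foreseen, but no number is given.

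**The concern.** The toxicity rate of a regimen needs the patients exposed to it as its denominator. The article does not leave the safety set open. It states an entry criterion, and that criterion does not on its face refer to exposure.

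The trial is open-label, so a patient assigned to neoadjuvant therapy may decline it and go straight to resection. Table 1 schedules adverse-event and living-state checks from the first weeks. One such check would put that patient into the safety set, although the patient was never at risk of drug or TACE toxicity. Conversely, a patient who has TACE and then withdraws before any assessment could be left out, because no further outcome data are collected after withdrawal ({18b}).

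At stake is the rate reported for the second objective. The mid-term analysis ({21b}) covers safety, and the data monitoring committee oversees it ({21a}). The per-protocol analysis in {20c} does not settle the matter, since it addresses the treatment effect and does not redefine the safety set.

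**Working it through.** **Inputs from the article**
- Entry rule for the safety set: {20a}, quoted above.
- Patients per arm: 30 (Sample size {14}).
- Safety outcome: grade 3 or higher toxicities ({12}).
- Non-adherence and switching: foreseen in {20c}, number not given.

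The article states no expected toxicity rate and no size for the safety set, so there is no figure of its own to reproduce here. The sample-size calculation does not bear on the point.

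**Assumed inputs**
- t, rate among exposed patients: 30% or 50%.
- b, grade 3 or higher rate that never-treated patients would show anyway: 0% or 20%.
- k, never-treated patients in the neoadjuvant arm who still have an assessment: 1 to 3.

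**Step 1: what the entry rule means.** The collection section ({18a}) places baseline assessments before randomization, so a measure after randomization is the natural counterpart, an assessment. The intervention section ({11a}) names each treatment and calls none of them a measure. The other reading, a therapeutic measure, is possible because of the verb *received*. Under it the set is already close to exposure-based and Steps 2 and 3 do not arise.

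**Step 2: never-treated patients admitted** (assessment reading, tabulation by assigned arm).

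Reported rate = [t(30 − k) + bk]/30 = t − k(t − b)/30.

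| t | b | k = 1 | k = 2 | k = 3 |
|---|---|---|---|---|
| 30% | 0% | 29.0% | 28.0% | 27.0% |
| 50% | 0% | 48.3% | 46.7% | 45.0% |
| 30% | 20% | 29.7% | 29.3% | 29.0% |
| 50% | 20% | 49.0% | 48.0% | 47.0% |

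The loss per patient is (t − b)/30. It is largest at b = 0: 30/30 = 1.0 point at t = 30%, and 50/30 = 1.7 points at t = 50%. At b = 20% it is 10/30 = 0.3 and 30/30 = 1.0 point. With k = 0 there is no change. If patients are grouped as treated, the never-treated leave the regimen's denominator and the dilution is zero.

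**Step 3: a treated patient dropped** (assessment reading, all 30 exposed, one with no later assessment).
- 15 events in 30 (50%) becomes 14/29 = 48.3% if the dropped patient had an event, or 15/29 = 51.7% if not.
- 9 events in 30 (30%) becomes 8/29 = 27.6% or 9/29 = 31.0%.

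This part can move the rate either way.

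**Step 4: scale.** The approximate 95% half-width for one arm of 30 is 1.96 × √[t(1 − t)/30]. It is 16 points at t = 30% and 18 points at t = 50%.

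**The case against.** The strongest reply is that a patient ordinarily receives a treatment and undergoes an assessment, so the sentence may already mean at least one treatment after randomization. That reading cannot be excluded. But if one sentence supports two safety sets, it fixes the set badly, and the same rewrite cures it.

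Second, a reader might infer that the regimen's toxicity is certainly understated. The article does not support that. Understatement needs the assessment reading, tabulation by assigned arm, at least one never-treated patient with an assessment, and t greater than b. The outcomes section counts grade 3 or higher toxicities generally, not only those attributed to the drugs, so a patient going straight to resection of a tumour of at least 10 cm can contribute events. Step 3 shows that the rate can also rise. This objection stands.

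Third, a reader might infer that control patients who switch to the drugs would carry toxicity into the surgery-alone arm, so that the difference between arms shrinks from both sides. That also goes too far. Intention-to-treat is stated for primary efficacy, and safety has its own sentence with no grouping rule. Silence on grouping in a journal article is not an error, since the full protocol may supply it. This objection stands too, and no contamination of the control arm is claimed.

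Fourth, the effect is small. Many patients who decline treatment may also withdraw and have no assessment. A shift of 1 to 2 points per patient is far inside the sampling error in Step 4, and the safety objective is exploratory, with no threshold. This limits the weight of the point but not the case for a one-sentence correction.

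**Conclusion.** The point holds in a limited form. The stated entry rule does not tie the safety set to receipt of trial treatment. Read as an assessment, it can admit neoadjuvant-arm patients who had no TACE, camrelizumab or apatinib, and can omit a treated patient who has no later assessment.

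If safety is tabulated by assigned arm, never-treated patients may dilute the regimen's grade 3 or higher rate by (t − b)/30 each, at most 1 point at t = 30% and 1.7 points at t = 50%. Three such patients would cost at most 3 or 5 points. The toxicity rate, the background rate, the number never treated and the grouping are all assumptions. Dilution is the likelier direction but not a certain one.

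This is a low-cost improvement to the safety analysis. It does not touch the primary endpoint.

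**What to change.** Replace the safety sentence in {20a} with:

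> The safety set is all participants who received any part of trial treatment (TACE, camrelizumab, apatinib or resection), grouped by treatment actually received. Rates of TACE and drug toxicity use participants who received at least one dose or procedure as the denominator.

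Report an assigned-arm table alongside, so that the randomized comparison stays visible.

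The cost is one sentence and one extra table, using exposure and adverse-event data the trial collects anyway. No clinical rule changes. The reported toxicity rate may come out slightly higher, and the as-treated groups are not strictly randomized, which is why the second table is needed. The change should be made before any safety data are tabulated by arm.

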### Interim analyses {21b}

Besides the final analysis, a mid-term analysis will be scheduled for this trial. The purpose of the mid-term analysis is about the safety and efficacy of the study. The scheduled time for mid-term analysis is set at 6 months after the last enrolled patient. If the RFS invalid hypothesis is rejected prior to teh final analysis, the trial might be discontinued.

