### Trial design {8}

The study is a prospective, multicenter, open-label, randomized controlled trial. Patients will be randomly assigned in a 1:1 ratio to either the experimental group (surgery after neoadjuvant treatment with TACE combined with camrelizumab and apatinib) or the control group (surgical resection without neoadjuvant treatment), using a parallel design with superiority.

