### Composition of the data monitoring committee, its role and reporting structure {21a}

The Data Monitoring Committee (DMC) is fully independent which is selected by internal criteria and responsible for overseeing the safety of the trial. The DMC met at the start of the trial and will meet quarterly for the trial’s duration.

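### The mid-term RFS test can end the trial with no boundary stated, and comes when stopping can only shorten follow-up

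*Protocol article*

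**What the plan says.** All references are to the protocol article.

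- **Interim analyses {21b}.** One mid-term analysis covers both safety and efficacy. On timing: "The scheduled time for mid-term analysis is set at 6 months after the last enrolled patient". On the consequence: "If the RFS invalid hypothesis is rejected prior to teh final analysis, the trial might be discontinued". I read the invalid hypothesis as the null hypothesis, since rejecting a hypothesis is the language of an efficacy test and not of futility. No nominal level, spending function or boundary is given.
- **Statistical methods {20a}.** The one threshold is that P "values < 0.05 are considered statistically significant".
- **Sample size {14}.** "Using an alpha of 0.025 at one-sided, a power of 80"%, with no mention of an interim look. The design rates are that "the 1-year RFS rate was 40% for patients with a single huge HCC after surgery", and that "neoadjuvant therapy could increase the 1-year RFS rate to 70"%.
- **Outcomes {12} and Table 1.** The primary endpoint is RFS at 1 year, and the last scheduled visit is month 12.
- **Recruitment {15}.** Enrolment takes 1.5 years and the study runs from January 2024 to June 2026. The final analysis therefore falls about 12 months after the last enrolment, and the mid-term look about 6 months before it.

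**The concern.** Two separate things look wrong.

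First, RFS is tested twice with a possible stop on rejection, and the stated levels are the full alpha. A reader who applies the article as written would use P < 0.05 on both occasions, which raises the chance of a false claim on the primary endpoint of a phase 3 trial.

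Second, an efficacy stop normally earns its place by sparing patients randomization to, or treatment with, the inferior option. Here the look comes after enrolment has closed and after planned treatment should have ended. What a stop would cut is follow-up, and it would cut it before every patient has reached the 1-year horizon of the primary endpoint. OS, a key secondary endpoint, would lose follow-up too. The article itself describes the sample as relatively small.

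**Working it through.** **Inputs.** 1-year RFS 40% and 70%, one-sided alpha 0.025, 80% power, 60 patients with 10% attrition, accrual 1.5 years (Sample size {14}). "Patients will be randomly assigned in a 1:1 ratio" (Trial design {8}). Study end at month 30 (Recruitment {15}). Interim at 18 + 6 = month 24 ({21b}). Assumptions not in the article: exponential survival, uniform accrual, final analysis at month 30.

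**The plan's own figure.** Yearly hazards are −ln 0.40 = 0.916 and −ln 0.70 = 0.357, so HR = 0.389. Schoenfeld events: 4(1.960 + 0.842)² / (ln 0.389)² = 35.3, so 36. A log-rank calculation with 1.5 years' accrual, 2.5 years in total and 10% loss spread over the study gives N = 60.0, which matches the article.

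**Information at the interim, follow-up to month 30.** Expected events per arm are 30 × [1 − (e^(−λ(T−1.5)) − e^(−λT)) / (1.5λ)].

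| | Control | Neoadjuvant | Total |
|---|---|---|---|
| T = 2.0 years (interim) | 19.7 | 10.6 | 30.2 |
| T = 2.5 years (final) | 23.5 | 13.7 | 37.2 |

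Fraction = 30.2/37.2 = 0.81 (0.84 if both arms have the control hazard).

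**Information at the interim, RFS capped at 12 months.** With uniform accrual, two thirds of patients (20 per arm) have 12 months at the interim. They contribute 20 × 0.60 = 12.0 and 20 × 0.30 = 6.0 events. The last third (10 per arm) have 6 to 12 months. Their mean probability of still being event-free is (e^(−0.5λ) − e^(−λ)) / (0.5λ), which is 0.507 in control and 0.766 in neoadjuvant, so they contribute 4.9 and 2.3 events. The total is 25.3 against 30 × 0.60 + 30 × 0.30 = 27.0 at the end. Fraction = 0.94.

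**Type I error if both looks use 1.96.** The two test statistics are bivariate normal with correlation √fraction. Error = 1 − P(Z₁ < 1.96, Z₂ < 1.96).

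| Case | Fraction | One-sided | Two-sided |
|---|---|---|---|
| Capped at 12 months | 0.94 | 0.031 | 0.062 |
| Followed to month 30 | 0.81 | 0.035 | 0.070 |

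Against 0.025 these are relative increases of about 24% (0.031/0.025) and 40% (0.035/0.025).

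**Who is still under treatment at month 24.** Control surgery is within 1 week of randomization. In the neoadjuvant arm, TACE is within 1 week, the drugs run about 2 months, and the preoperative CT is 14 ± 7 days after the last dose (Intervention description {11a}). That is roughly 10 to 13 weeks to the preoperative assessment, against at least 26 weeks since randomization for every patient. No upper limit is stated for the date of surgery, so a delayed operation is possible but not planned.

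**Who would be short of the endpoint.** Of the 20 patients with under 12 months, the expected number still event-free is 10 × 0.507 + 10 × 0.766 = 12.7 (21% of 60). With both arms at the control rate it is 20 × 0.507 = 10.1 (17%).

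**The case against.** The strongest reply is that the article condenses a full protocol. A boundary and its spending function are commonly placed in that document or in the analysis plan. The P < 0.05 sentence is a general one that also covers t-tests and chi-square tests; it is not written as the interim rule. This stands. A reader might infer that the false-positive rate definitely exceeds 0.025, but the article supports only the conditional statement: no boundary is stated, and the levels that are stated would inflate the error if used twice.

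A reader might also infer from the reproduced N = 60 that the design has a single look. It does not show that. One-sided 0.025 can equally be the overall alpha of a two-look plan, and O'Brien-Fleming-type spending with 60 patients still gives 81.3% power on the month-30 calculation.

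A third tempting reading is that stopping would lose the 1-year endpoint in a third of patients. A third would have under 12 months' follow-up, but many of them would already have had an event, and Kaplan-Meier and Cox methods use the censored time of the rest. In the capped case only about 6% of the expected 1-year events are outstanding.

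On size, Table 1 schedules no visit after month 12, so 0.031 is the better supported figure; 0.035 needs follow-up beyond that.

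Finally, the look also serves safety, the article says only that the trial might stop, and an earlier result has some value. All true, but none of it gives the efficacy stop a benefit to enrolled patients. The DMC is described as "responsible for overseeing the safety of the trial", and one might conclude that nobody independent would see the efficacy look. The article does not assign that look, but this is charter-level detail and the steering committee has independent members, so I do not rest the point on it.

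**Conclusion.** The point holds in two parts of different strength.

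**Timing: high confidence, whatever an unseen document says.** At the planned look all 60 patients are randomized and planned treatment should have ended about 3 months after randomization. An efficacy stop spares no randomization and no planned treatment. It gains about six months and leaves an expected 10 to 13 of 60 patients event-free without a full year of follow-up.

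**Alpha: medium confidence and conditional.** If the stated levels are used at both looks, one-sided error is about 0.031, and at most about 0.035, instead of 0.025. The inflation is moderate because the look is late. These figures rest on exponential survival, uniform accrual and a final analysis at month 30.

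This should be fixed, and before the mid-term analysis is run, because alpha cannot credibly be repaired once RFS has been compared between arms.

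**What to change.** **Preferred.** Remove the efficacy stop from {21b}. State that the only confirmatory test of RFS is the final analysis, done once all patients have 12 months of follow-up, and keep the mid-term look for safety. This takes a few sentences and gives up only a possible declaration about six months earlier.

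**If the efficacy look stays.** State the boundary and require 12-month follow-up to be completed whatever the look shows. Two examples:

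- O'Brien-Fleming-type spending: two-sided p < 0.026 at the interim and p < 0.0425 at the end for a fraction of 0.81, or about 0.041 and 0.039 for 0.94. At 0.81, power with 60 patients falls from 82.1% to 81.3%, a loss of 0.8 point.
- Haybittle-Peto: two-sided p < 0.001 at the interim. This uses 0.0005 one-sided, so even simple subtraction leaves 0.025 − 0.0005 = 0.0245 for the final test.

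The text should also say whether RFS is analysed to 12 months or to study end, since the fraction and hence the spending levels depend on it. If the full protocol or analysis plan already holds a boundary, citing it in {21b} settles the alpha part. The timing part would still need the change above.
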